#### Analysis of secondary endpoints

For evaluating physical training as potential modulator of cognitive training gain transfer, correlations between fitness changes and integrity changes of the corpus callosum will be applied. Moreover, an interaction between corpus callosum integrity and fitness changes with respect to transfer will be considered in a logistic regression model. Such an interaction can be expressed as a correlation between fitness changes and the degree of transfer in a group with low/high corpus callosum integrity.

To evaluate the predictive value of brain vascular lesion, cortical amyloid load, higher Default Mode Network activity, and genetics for transfer of cognitive training gains in HOA, a logistic regression model with transfer as the dependent variable is used. All effects of the potential predictors are included as main effects. Additionally, to adjust for ACT, ACT and all interactions with ACT are included in the model as independent covariates.

To determine the impact of ACT on the structural integrity of the corpus callosum, Default Mode Network activity, BDNF, motor fitness, and VO_2_peak/VO_2_max, logistic regression models for these variables are fitted. ACT will be included as an independent variable. Additionally, the model will be adjusted for all other variables and the interactions with ACT. For example, the model for structural integrity of the corpus callosum will include ACT, Default Mode Network activity, BDNF, motor fitness, VO_2_peak/VO_2_max and all interactions with ACT as independent covariates.

Similar models will be fitted to examine the association between baseline physical activity and the structural integrity of the corpus callosum, Default Mode Network activity, and BDNF. Here, baseline physical activity and all possible interactions with baseline physical activity will be additionally included as independent covariates.

To build a robust individual index of transfer likelihood based on all potential predictors and interactions, a multimodal, high-dimensional dataset needs to be analyzed. For this purpose a regularized logistic regression for transfer will be performed including all potential predictors and relevant interactions. Specifically, to automatically select relevant covariates, a componentwise likelihood boosting approach will be used. To better detect potentially complex patterns in the multimodal data that are linked to transfer, a deep learning approach will be employed; specifically, deep Boltzmann machines [71]. This specific approach will potentially allow for the detection of non-linear relations and interactions while still providing type 1 error control, and results in an integrated statistical model for transfer prediction.

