### Statistics

#### Sample size

Primary outcome: the analyses will focus on training gain transfer (defined as a binary criterion for each subject) and simultaneously incorporate measures of corpus callosum integrity and bihemispheric processing. The sample size calculation was performed based on main effects analyses where the effects of both measures will be considered as main effects. Assuming a transfer rate of cognitive training gains of about 15% for participants with low corpus callosum integrity, and a transfer odds ratio of 3 for participants with high corpus callosum integrity, a sample size of 160 provides a power of 0.8 at a significance level of 0.05 for a Wald Test in a logistic regression model. Assuming a dropout rate of about 15%, a total of 192 participants need to be included.

Secondary outcome: for evaluating physical training as a potential modulator of cognitive training gain transfer, ACT-induced fitness changes will be analyzed with respect to changes of corpus callosum integrity, as well as with respect to effects on transfer. The former analysis corresponds to considering the correlation between fitness changes and integrity changes. For the latter, an interaction between corpus callosum integrity and fitness changes with respect to transfer will be considered in a logistic regression model. Such an interaction can be expressed as a correlation between fitness changes and the degree of transfer in a group with low/high corpus callosum integrity. Based on the results by Voss et al. [14], we assume a correlation of about 0.43 between both measures. At a significance level of 0.05, 30 individuals per (equally sized) integrity group are needed to detect such a correlation with a power of 0.8. As a result, ACT needs to be performed for 60 individuals in total. Assuming a dropout rate of about 15%, 72 subjects at the German Sport University Cologne will undergo the extended experimental protocol.

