#### Definition and analysis of primary endpoint

The primary endpoint is defined as the dichotomous outcome training gain transfer (Yes/No). Successful transfer will be defined as: (1) Performance improvement in a logical reasoning training task from the second to the last training session, (2) performance improvement in an untrained fluid intelligence transfer task (Leistungsprüfsystem, subtest 4) from the pre-cognitive-training phase to the post-cognitive-training phase, and (3) maintenance of the performance in the transfer task from post-cognitive-training phase to follow-up. Transfer task performance alterations have to be numerically greater than the mere retest effect of an untrained control group.

The primary endpoint will be analyzed using a logistic regression with measures of corpus callosum integrity and bihemispheric processing as independent variables. As a primary analysis, the effects of both measures will be considered as main effects. In subsequent analyses, we will take into account that bihemispheric processing may not be necessary for all participants, whereby strong training performance might specifically indicate such participants. This will be incorporated into the analyses by interaction terms and by allowing for non-linear effects. The models will be adjusted for age. In the primary analysis subjects with missing values will be excluded. Sensitivity analysis will be performed to evaluate the impact of the missing values.

The primary population is the intention-to-treat population. As a sensitivity analysis, an as-treated analysis will be performed. To investigate the center effects, center number will be additionally incorporated into the models.

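### The 0.8 power claimed for the ACT modulation analysis belongs to a correlation within one integrity group, not to the planned interaction on Yes/No transfer

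*Protocol article*

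**What the plan says.** The secondary part of the Sample size section names the test: "an interaction between corpus callosum integrity and fitness changes with respect to transfer will be considered in a logistic regression model". Analysis of secondary endpoints repeats it. Both sections then add the same gloss: "Such an interaction can be expressed as a correlation between fitness changes and the degree of transfer in a group" with low or high integrity.

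The numbers rest on that gloss. The protocol states "we assume a correlation of about 0.43 between both measures", citing a published study, and continues: "At a significance level of 0.05, 30 individuals per (equally sized) integrity group are needed" to detect that correlation with power 0.8. It concludes: "As a result, ACT needs to be performed for 60 individuals in total". With 15% dropout this becomes 72 recruited in Cologne.

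Transfer itself is binary: "The primary endpoint is defined as the dichotomous outcome training gain transfer (Yes/No"). No graded version of it is defined anywhere.

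**The concern.** Two different quantities are treated as one. The interaction asks whether the relation between fitness change and transfer differs between the low- and high-integrity groups. A correlation inside one group is a simple effect and carries no information about a difference. The protocol specifies no difference between groups.

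The outcome also changes scale. The model is logistic on a Yes/No outcome, while the power figure uses a correlation with an undefined degree of transfer.

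This calculation is the stated justification for giving ACT to 60 completers (72 recruited), each with a 20-week physical training period. A reader who believes the interaction was tested with power 0.8 would take a null result as fair evidence against modulation. With the power shown below, a null result would say little.

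**Working it through.** **Inputs from the protocol.** Alpha 0.05, sidedness not stated; power 0.8; r = 0.43; 30 per integrity group (all from Sample size, secondary outcome). Transfer rate 15% at low integrity and odds ratio 3 at high integrity (Sample size, primary outcome). The high-integrity rate follows: odds 0.15/0.85 × 3 = 0.529, so 0.529/1.529 = 34.6%. An alternative common rate is the 22% stable transfer (9 of 41) in the Background.

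**Assumption not in the protocol.** The correlation in the other group. I take 0 and show a range.

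**1. The protocol's own figure.** Single correlation against 0, Fisher z: atanh(0.43) = 0.4599.
- Two-sided: n = ((1.960 + 0.842)/0.4599)² + 3 = 40.1, so 40 to 41. Power at n = 30: Φ(0.4599 × √27 − 1.960) = Φ(0.430) = 0.67.
- One-sided: n = ((1.645 + 0.842)/0.4599)² + 3 = 32.2. Power at n = 30: Φ(2.390 − 1.645) = 0.77.

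The figure of 30 is therefore approximately reproduced only with a one-sided test, which is not stated. Dropout: 60/0.85 = 70.6, close to the stated 72.

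**2. The interaction on a continuous scale.** With 30 per group, the standard error of a difference of two Fisher z values is √(2/27) = 0.2722. For r = 0.43 against 0: 0.4599/0.2722 = 1.69.
- Two-sided power: Φ(1.69 − 1.96) = 0.39.
- One-sided power: Φ(1.69 − 1.645) = 0.52.
- For two-sided power 0.8: n = 2 × (2.802/0.4599)² + 3 = 77.2, so 78 per group.

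Range over the other group's correlation (two-sided, 30 per group):

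| r in other group | Power |
|---|---|
| 0.43 | no interaction exists |
| 0.2 | 0.16 |
| 0.1 | 0.26 |
| 0 | 0.39 |
| −0.29 | 0.80 |
| −0.43 | 0.92 |

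To reach 0.8, greater fitness gains would have to go with less transfer in one of the two groups.

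**3. The interaction as planned, on binary transfer.** Simulated logistic regression with a two-sided Wald test of the product term, 30 per group, r = 0.43 in one group and 0 in the other:

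| Transfer rates | 0.43 as latent correlation, then dichotomised | 0.43 as correlation with the Yes/No outcome itself |
|---|---|---|
| 15% / 34.6% | 0.15–0.19 | 0.26–0.31 |
| 22% / 22% | 0.17–0.19 | 0.32 |
| 50% / 50% (favourable assumption) | 0.25–0.28 | 0.35–0.36 |

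The spread within a cell reflects which group carries the correlation and simulation error.

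**The case against.** **The correct model is named.** The logistic interaction is the stated analysis. The correlation sentence is an explanatory gloss and the basis for the power figure. This stands. A reader might infer that the interaction test has been replaced by within-group correlations, but the protocol does not say so.

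**No rule for comparing groups is stated.** A reader might infer that modulation will be declared when the correlation is significant in one integrity group and not in the other. Under that rule, with r = 0.43 in both groups, exactly one would be significant in about 2 × 0.666 × 0.334 = 44% of trials (two-sided). The protocol does not describe this rule, so the 44% is not an error rate of the plan. Nor does formally comparing two group correlations generate many false interactions. With equal log-odds slopes and rates of 15% and 34.6%, such a test rejected in 6–7% of simulated trials. It rejected in 9–22% only under an assumed unequal spread of fitness change.

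**The low power depends on assumptions.** This also stands: r = 0 in the other group and two-sided testing are mine, and a full sign reversal would give 0.92. However, the protocol hypothesises that coordination training acts positively on transfer, and nothing in it supports a reversal.

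**The objective is secondary.** The primary hypothesis and its calculation of 160 do not depend on this sentence. The companion correlation between fitness change and integrity change can use all 60 completers. If r = 0.43 applied there, power would be Φ(0.4599 × √57 − 1.96) = 0.93. That softens the consequence but does not make the 0.8 right for the interaction.

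**Conclusion.** Wrong as written. The interaction cannot be expressed as a correlation within one integrity group, and the 0.8 with 30 per group does not apply to the planned test. This part needs no outside assumption, because r = 0.43 in both groups satisfies everything stated and leaves no interaction to find.

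The size of the shortfall does rest on assumptions. With r = 0.43 against 0, power is 0.39 two-sided (0.52 one-sided) on a continuous scale. For the logistic product term it is roughly 0.15 to 0.20 if 0.43 is a latent correlation at the protocol's own transfer rates, and up to about 0.36 under more favourable scaling. Even for a single correlation, 30 gives 0.67 two-sided or 0.77 one-sided. The correction is worth making, but it concerns a secondary objective and leaves the primary analysis untouched.

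**What to change.** - Delete the equivalence sentence in both Sample size and Analysis of secondary endpoints.
- Base any claim of modulation only on the integrity by fitness-change product term in the stated logistic model, reported with its confidence interval. Label that analysis exploratory.
- Report within-group correlations as descriptive.
- Replace the 0.8 with a power figure computed for the test actually fitted, giving the assumed correlation in each group, the outcome scale and the sidedness. Alternatively, say that 0.8 refers only to a single within-group correlation, and correct it for sidedness. The 0.39 above comes from comparing two groups of 30 and should not be attached to a model with continuous integrity.
- A continuous gain on the transfer task (Leistungsprüfsystem, subtest 4) may be added as a supportive outcome. It should not replace the defined Yes/No transfer, which also requires improvement in the training task and maintenance to follow-up.

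Cost: a text change and a less favourable power statement for a secondary objective. No additional participants or data are needed.

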## Background

### Scientific background

Cognitive health has been consistently quoted as significant for life quality by older people and is regarded as an important contributor to late-life functioning [1, 2]. Patterns of cognitive change show great variation in healthy aging [3]. Cognitive training might contribute to enhance or preserve cognitive skills in cognitively healthy older adults (HOA). While improvements in cognition through training have been reported frequently in HOA, the capability to transfer cognitive training gains decreases with age [4–8]. Ideally, cognitive training would not only improve the function of trained cognitive tasks but also of untrained tasks of the same or a different cognitive domain (i.e., transfer of training gains). There is little evidence for successful transfer of cognitive training effects in HOA [6, 9]. Moreover, although transfer has been the subject of research for many years [10] the neurobiological mechanisms underlying the complex capability of transfer are still unknown. We recently demonstrated successful transfer of logical reasoning training gains to fluid intelligence immediately after a 4-week training in 71% of the HOA (*N* = 29 out of 41), but this effect persisted only in a subgroup of 22% over a 3-month follow-up period (*N* = 9 out of 41) [11].

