### Objectives

#### Primary objective

Four types of transfer training interventions have been described: strategy-based (e.g., logical reasoning), multimodal (complex, often social or lifestyle interventions), cardiovascular (i.e., physical training), and specific cognitive process-targeted training interventions (e.g., working memory) [16]. Transfer effects differ between transfer types but share a common feature: transfer effects decline with age [16]. To date, little is known about the neural mechanisms of transfer [16]. Specifically, the mechanisms of either maintenance or age-related decrease of transfer of cognitive training gains in HOA are largely unknown. Increased bihemispheric cooperation can reliably be seen with increasing processing demands in young adults and, as we showed, already on lower levels of cognitive demand in HOA [17]. This compensatory increase of bihemispheric processing in HOA is known as the concept of Hemispheric Asymmetry Reduction in Older Adults (HAROLD) [12]. This phenomenon could be the functional link between the observed association of transfer capabilities and structural integrity of the corpus callosum. Beyond pure compensation, HAROLD may serve as a mechanism enabling the structurally and functionally altered aged brain to use alternative neural circuitry and thereby to re-establish more efficient lateralized processing during learning [16]. Hence, increased bihemispheric cooperation/HAROLD, based on the structural integrity of the corpus callosum, may indeed be a functional mechanism mediating transfer capabilities in HOA.

Main research goal of the AgeGain study is to investigate the neurobiological mechanisms of transfer of cognitive training gains in detail by elaborating brain network capabilities representing transfer using a multimodal-neuroimaging approach in HOA. Specifically, the following primary hypothesis will be tested: Structural integrity of the corpus callosum (high / low) and bihemispheric cooperation (reduced / increased) will predict successful transfer of cognitive training gains in HOA. The association of corpus callosum integrity with transfer capability will be determined by diffusion-tensor imaging (DTI) measures of structural integrity / connectivity, mainly fractional anisotropy (FA) of the corpus callosum, see Fig. 2a. The association of bihemispheric processing and transfer capability will be determined using task-related functional magnetic resonance imaging (fMRI) (see Fig. 2b).

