
In sum, aerobic exercise – and coordination exercise training are associated with positive structural and functional brain changes as well as improvements of cognitive performance in HOA. Moreover, cerebral regions targeted by these interventions are primarily involved in age-related cognitive decline including the corpus callosum, the hippocampus, frontal and temporal cortices, and the Default Mode Network. As a secondary outcome, we will determine if physical training, comprising aerobic and coordination components, modulates transfer of cognitive training gains in HOA. Moreover, we will determine the impact of baseline physical activity on transfer in HOA.

Subcortical cerebrovascular lesions reflected in white matter hyperintensities and cortical β-amyloid aggregation are highly prevalent and strongly age associated with central nevous system (CNS) pathologies [45]. Both findings are suspected to have a deleterious effect on neuronal function. White matter hyperintensities have been found to affect structural connectivity in the brain on the subcortical level [46]. Amyloid pathology, on the other hand, which is a hallmark of Alzheimer’s disease [47], has been discussed to affect regional synaptic function on the cortical level [48]. Although both findings have been associated with manifest cognitive decline or dementia, they are known to be present in a significant proportion of the cognitively healthy elderly, potentially leading to subclinical deficits [49, 50]. White matter hyperintensities frequently observed in the prefrontal cortex in clinically HOA have been linked to subclinical disturbances of executive function, whereas cortical amyloid deposition has been associated with a minor decline in memory function in this population [51]. Transfer capability represents a multidimensional cognitive function which requires executive and memory skills and presumably depends on highly efficient neuronal pathways including bihemispherical communication. Thus, the two mentioned pathologies are supposed to have a cumulative negative effect on transfer performance, even ahead of other cognitive symptoms. Consistently, as a further secondary outcome, the study aims at investigating white matter hyperintensities and cerebral amyloid burden as potential modulators of transfer of cognitive training gains in HOA.

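### The secondary model of transfer on vascular lesions and amyloid load adjusts for ACT but not for age, so part of the age effect can be credited to these two pathologies

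*Protocol article*

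**What the plan says.** In the protocol article, the section Analysis of secondary endpoints specifies the model for vascular lesion, amyloid load, Default Mode Network activity and genetics:

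- Outcome: "a logistic regression model with transfer as the dependent variable is used".
- Predictors: "All effects of the potential predictors are included as main effects".
- Adjustment: "Additionally, to adjust for ACT, ACT and all interactions with ACT are included in the model as independent covariates".

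Age is not in this list. The statement "The models will be adjusted for age" stands one section earlier, under Definition and analysis of primary endpoint. It follows the models of corpus callosum integrity and bihemispheric processing, and nothing carries it over to the secondary models.

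Elsewhere the article relates age to both sides of the secondary model:

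- Secondary objectives describes white matter hyperintensities and cortical amyloid as "highly prevalent and strongly age associated".
- Primary objective says that "transfer effects decline with age".
- Scientific background says that "the capability to transfer cognitive training gains decreases with age".

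On purpose, Table 1 speaks of predictive value. Secondary objectives presents the two pathologies as potential modulators of transfer, and the Discussion expects the trial to help determine their impact.

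**The concern.** On the article's own account, age is associated with two of the predictors and with the outcome. A model that omits it lets a lesion or amyloid term pick up part of the age effect. The distortion runs in the direction the investigators expect (more pathology, less transfer), so a spurious result would look like confirmation. Design does not hold age constant: entry is from 60 years with no upper limit.

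For a purely predictive marker, leaving out age is not an error in itself. For a claim that the pathology modulates transfer, the effect has to be separated from that of age. The article makes both kinds of claim.

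**Working it through.** **The plan's own figure.** The article gives no figure for the secondary model. Its primary sample size supplies the inputs.

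- Transfer rate with low integrity: p1 = 0.15. Odds 0.15/0.85 = 0.1765; times the odds ratio of 3 = 0.529; p2 = 0.529/1.529 = 0.346.
- Two-sided Wald test, equal groups: n per group = (1.960 + 0.842)² × [1/(0.15 × 0.85) + 1/(0.346 × 0.654)] / (ln 3)² = 7.849 × 12.26 / 1.207 = 79.7.
- Total 159.5, so 160. The stated figure reproduces and is not in dispute.

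Taken from the document: N = 160, an average transfer rate of (0.15 + 0.346)/2 = 0.248, and 60 subjects with ACT.

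**Assumed, because the document gives no values.** Correlation r of age with each of lesion and amyloid: 0.2 to 0.5. Odds ratio for transfer per SD of age: 0.7 to 0.5. Neither pathology has any effect given age.

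**Size of the spurious effect (first-order approximation).**

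- One marker alone, without age: log odds ratio ≈ r × ln(OR for age).
  - r = 0.3, OR 0.7: 0.3 × (−0.357) = −0.107, odds ratio 0.90 per SD.
  - r = 0.5, OR 0.5: 0.5 × (−0.693) = −0.347, odds ratio 0.71 (0.72 in simulation).
- Lesion and amyloid together, linked only through age (mutual correlation r²): log odds ratio of each ≈ r/(1 + r²) × ln(OR for age).
  - r = 0.3, OR 0.7: 0.275 × (−0.357) = −0.098, odds ratio 0.91.
  - r = 0.5, OR 0.5: 0.400 × (−0.693) = −0.277, odds ratio 0.76.

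**False-positive rate in the model as specified (simulation).** The model contains lesion, amyloid, network activity and one binary genotype (prevalence 25% assumed) as main effects, plus ACT coded 0/1 and all ACT interactions. The test is a two-sided 5% Wald test of the lesion main effect. There were 2,000 trials per cell, and the 2 to 3% of fits that did not converge were dropped. Each cell shows the rate without age / with age.

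| r | age OR 0.7 | age OR 0.6 | age OR 0.5 |
|---|---|---|---|
| 0.2 | 7.0% / 5.6% | 6.2% / 4.2% | 8.6% / 4.9% |
| 0.3 | 7.1% / 5.0% | 8.0% / 4.8% | 11.2% / 5.9% |
| 0.4 | 9.5% / 5.3% | 10.5% / 5.2% | 14.9% / 4.9% |
| 0.5 | 8.3% / 4.8% | 12.6% / 4.7% | 17.6% / 4.9% |

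Over r = 0.3 to 0.5 this is about 7 to 17%. Repeat runs put the top corner at 17 or 18%, and the Monte Carlo standard error there is under one percentage point. With a weaker age effect (OR 0.8) and r = 0.2 the rate was 5.3%.

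**Comparison.** A model with a single marker and nothing else gives about 9 to 40% over r = 0.3 to 0.5 and age OR 0.7 to 0.5. The joint model gives less for two reasons. Amyloid absorbs some of the age effect. With 0/1 coding and interactions, the lesion main effect rests on the 100 subjects without ACT. The lower rate therefore reflects less precision as well as somewhat less bias.

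**The case against.** The strongest case on the other side has four parts.

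1. **This is a condensed article.** Covariate detail for secondary models often sits in an analysis plan, and age is adjusted for in models of the same outcome. It is true that a deliberate exclusion of age is not shown. But the covariate list is written out here and names one adjustment, so the model is fixed without age rather than left open.

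2. **The aim is prediction.** Table 1 and the analysis section speak of predictive value, for which an unadjusted marker is legitimate. This stands for that reading. It does not cover the modulator reading in Secondary objectives.

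3. **The sizes are assumed.** No age correlation is given. Restricting entry to people aged 60 and over, without cerebrovascular or cognitive illness, brain lesions or diabetes, may weaken the age-pathology association. This stands, and the lower part of the range deserves weight.

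4. **Only some terms are affected.** A reader might infer that every secondary model is confounded by age. The document does not support that. It makes no direct statement linking age to Default Mode Network activity, genotype or baseline physical activity. Allocation to experimental or control groups is random within site, so no confounding of ACT by age is shown. Callosal integrity does fall with age (Fig. 1), but that is only one arm of a confounding path in the baseline-activity models.

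**Conclusion.** The point holds for the vascular-lesion and amyloid terms of the secondary transfer model. The covariate set as written omits a variable that the article itself ties to both predictor and outcome, while the article interprets these terms as modulators. Under the assumed ranges (r 0.3 to 0.5, age OR 0.7 to 0.5 per SD), a term with no effect of its own shows a spurious odds ratio of about 0.91 to 0.76 per SD. It is falsely significant in about 7 to 17% of trials, against about 5% with age included. At r = 0.2 the rate is about 5 to 9%.

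Two stronger readings are tempting and not supported. One is that age will be reported as a pathology effect: only part of the age effect can be, by an amount the document does not let us fix. The other is a false-positive rate of 40%, or even 70% if the age odds ratio is taken down to 0.33 per SD. Those figures belong to a single-marker model, which is not the one specified.

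The primary analysis is unaffected, since it already adjusts for age. This is a clarification worth making to a secondary analysis.

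**What to change.** In Analysis of secondary endpoints, state that age enters the secondary logistic model of transfer as a continuous covariate, as in the primary-endpoint models. Report the lesion and amyloid effects both with and without age: the unadjusted estimate serves the predictive reading, the adjusted one the modulator reading.

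The cost is one sentence and one degree of freedom. Age is an entry criterion and so is known for every subject; no new data are needed. Adding age to the ACT and baseline-physical-activity models is optional, because the document does not show age confounding there.
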